### 13.4.2 Responsibilities of the Principal Investigator

The Principal Investigator is in charge of the following procedures:

- Approval by the local Ethical Committee
- Recruitment of subjects in accordance with inclusion and exclusion criteria.
- Provision of informed consent signed by the parents / caregivers of the children
- Dispensation of study formula to the subjects
- Destruction and documentation of destruction of unused formula after study termination
- Compliance with the defined procedures in accordance with the “European Good Clinical Practice” (GCP)
- Treatment of all subjects in accordance with the protocol from start to study termination
- Complete and exact filling in of all Case Report Forms
- Organisation of sample shipment to Germany in coordination with the team at LMU Munich, Germany.
- Good cooperation with the monitor. The monitor has to be provided with original data, which are treated confidential.
- Data entry from CRF into computerized data base
- Announcement of all serious adverse events to the sponsor (HiPP GmbH) and the Chief Investigator ([name]. [name]).
- Retention of records: storage of all original data after completion of the study report for 15 years at the appointed location
- Confidential handling of all information coming up in the context of the study.
- Correct use of goods and money made available for the study.
- A deputy can be nominated by the Principal Investigator. Nevertheless the main responsibility stays at the Principal Investigator.
- Generation of final study report and publication in coordination with the Chief investigator.

### 13.4.3 Responsibilities of the Sponsor

- Supply of study formula in sufficient amounts free of charge
- Supply of incentives for all subjects that terminate the study in accordance with the protocol
- Supply of study protocol and all necessary documents
- Announcement of serious adverse events effects according to the national law (Serbia; Ethical committee)
- Insurance coverage in accordance with the existing law
- Payments as agreed on in the respective agreements
- Retention of records: storage of all original data after completion of the study report for 15 years at the appointed location

**13.4.4 Responsibilities of the Chief Investigator (LMU) and team**

- Study supervision
- Study management / support of study organisation at the site in Belgrade (GAK “Narodni Front” Hospital for Gynaecology and Obstetrics, Belgrade, Serbia)
- Monitoring
- Primarily responsible for data entry, data management and data evaluation (might be done in coordination with the team in Belgrade)
- Verification of sufficiency of documentation
- Statistics
- Laboratory analysis: plasma amino acid profiling, fatty acid profile
- Provision of a study report within 3 months after all analyses done in coordination with Principal Investigator
- Publication of results in a scientific magazine in coordination with Principal Investigator if suitability (right quality) of data is given.
- Retention of records: storage of all original data after completion of the study report for 15 years at the appointed location

**13.4.5 Abnormal termination of the study**

If the study has to be stopped, the Principal Investigator as well as its team will be informed in a written form. All documents related to the study will be sent back to the sponsor. Study formula will either be sent back to the sponsor or will be destroyed. In case of abnormal study termination the ethical committee needs to be informed by the Principal investigator not later than 15 days after abruption.

# **Formula with modified content of protein and improved fatty acids and their impact on infant growth and health**

## **Study nr: 502042**

### **Amendment No.1**

During the implementation of the study at the Clinical Centre Belgrade, it turned out that for two aspects the actual situation differs from assumptions on which the study protocol (Ver. 03.11.2009) is based. Thus, the following changes are required:

#### **1. Rescheduling of the baseline visit**

- Status quo: According to the study protocol the baseline visit is performed on postnatal days 4 or 5.
- Changes to study protocol: Instead of performing the baseline visit on postnatal days 4 or 5, the baseline visit is performed on postnatal days 3 or 4 (day of birth = postnatal day 0).
- Reason: Contrary to the initial assumption, most of the mothers, who delivered vaginally, leave the hospital already on postnatal day 3. Thus, these infants would be lost as potential study subjects and the study could not be completed on time.
- Background: During the first week of life biochemical parameters change rapidly, thus we aim for a narrow time window of sample collection. This narrow time window is maintained after rescheduling of the baseline visit.

#### **2. Change of procedure for the enrollment of infants for the breast fed group in the course of the study**

- Status quo: According to the study protocol infants are enrolled on postnatal days 3 or 4 independent of the parental intention to breast feed or not and 100 breast fed infants and 200 formula fed infants shall be studied (equal group sizes in the breast fed reference group and the two randomized formula groups)
- Amendment to study protocol: Once 100 breast fed infants have passed visit 1, no more infants will be enrolled for the breastfeeding group and no more breastfed infants will participate in visits 1 to 4.
- Reason: Contrary to the initial assumption the percentage of mothers who breast feed beyond day 28 is about 70%. Thus the predefined number of

subjects in the reference group (100 breast fed infants, who completed the study according to protocol) can be expected to be reached much earlier than the completion of the formula groups.

- Background: Infants have to be enrolled into the study on postnatal days 3 or 4 (baseline visit). But randomization into one of the formula groups can take place until postnatal day 28, if parents have meanwhile opted for formula feeding. Thus, it is unknown at time of enrollment, whether the infant will become eligible for one of the randomized formula groups. On the other hand, the time until the number of necessary subjects in the study groups is achieved may differ considerably between the groups. Considering the high percentage of breast feeding we expect the reference group to be completed much earlier. In case enrolled subjects are breastfed beyond postnatal day 28 they should not participate in study visits 1 to 4 once 100 infants have passed visit 1 in this group, furthermore no more subjects should be enrolled for the breastfeeding group. This would not be justified for ethical reasons and not possible for logistical and budgetary reasons.
- Practical implementation: At time of enrollment all parents will be informed that it is possible that the participation of their child will be terminated if the number of necessary subjects has already passed visit 1 in the corresponding study group. This will be documented in the case report form for visit 1 giving the reason: “excluded, because maximal participant number in the group meanwhile achieved”. The infants will not participate in visits 1, 2, 3 and 4, but they will not be designated drop outs, as it was not the decision of the families to terminate participation. Collection of the baseline data will allow to test, whether the infants studied until visit 4 are representative for all enrolled infants. Whenever 100 subjects have passed visit 1, no more subjects will be enrolled in the breastfeeding group.

## **Formula with modified content of protein and improved fatty acids and their impact on infant growth and health Study nr.: 502042**

### **Amendment No.2**

During the implementation of the study at the Clinical Centre of Serbia in Belgrade, it turned out that for the following aspect the actual situation differs from assumptions on which the study protocol (Ver. 03.11.2009) including Amendment version 1.1 is based. Thus, the following changes are made:

#### **Omission of blood sampling at the baseline visit and changes regarding the window for performing the baseline visit**

- Status quo: According to the study protocol a blood sample is taken at the baseline visit (postnatal days 3 to 4) to determine:
  - ✓ full blood count with differential, C-reactive protein, Astrup, electrolytes Na / K / Cl, Glucose, total bilirubin and protein
  - ✓ serum albumin, serum creatinine, blood urea nitrogen
  - ✓ plasma amino acid profile, plasma phospholipid fatty acid profile
- Change to study protocol: the blood sampling at baseline visit will be skipped. All other data assessments at the baseline visit will be maintained (see study protocol: chapter 8.5.1, page 36). The window for performing the visit is changed from postnatal days 3 to 4 to a wider window between birth and postnatal day 14 or before day 28 at the latest, if the investigator is sure that the subject is still able to shift to full formula feeding.
- Reason: For the success of the study 100 infants per group need to be enrolled (100 breast fed; 100 control formula fed and 100 modified formula fed). The enrollment is competitive which means if in one group 100 infants are enrolled no more subjects will be enrolled into this group. As the breast fed group is completed no more subjects are to be enrolled into this group.

To reduce the number of blood withdrawals the blood draw on baseline visit is skipped as it is estimated that approx. 6 infants have to pass the baseline visit (including blood sampling) for each infant randomized into a formula group (problem of available resources and ethics). Thus, an adaption of the study protocol is required and is considered possible without sacrificing major scientific aims of the study. A comparison of the clinical data at baseline between the groups can be performed, which permits the exclusion of major differences between the groups. For the statistical analysis of biochemical parameters at study end the adjustment for baseline values obtained during the first postnatal days is not considered mandatory. A wider window for the

performance of the baseline visit does not cause a loss of data as the collected information is either independent of time or is obtained retrospectively from hospital records. On the other hand, this is expected to increase the participation rate.

- Practical implementation:
  - **Screening** for eligible formula-subjects is performed in the center by study team members on the maternity ward
    - complete the „screening-list“
  - **Personal contact** with potential subjects: in case of interest
    - check for inclusion and exclusion criteria
    - verbal information for interested parents (duration, visits, blood sampling at the end of the study);
    - hand over printed „parents information“ and “informed consent” / “accept form”
  - **in case of decision to participate in the study immediately after screening:**
    - detailed explanation of the study
    - after clarification of all open questions signature of informed consent (if parents decide not to sign this is recorded in the screening list and personal information is deleted)
    - If subject is suitable to the study and in case the family wants to formula feed / is already feeding formula an appointment for the baseline visit should be made (parents need to be called / contacted for scheduling the baseline visit).
    - randomization and distribution of study formula with corresponding randomization number
    - complete “subject identification list” and “subject randomization list” (subject randomization number will be transferred from HiPP ambulance)
    - performance of baseline visit without blood sampling, but otherwise according to original protocol
  - **in case parents wish to decide about participation later:**
    - ask for contact data / telephone number (“accept form” to be filled out, signed by parents).
    - inform parents that they will be called within the next week by a member of the study team
    - do not perform baseline visit in the clinic

- call parents and ask for interest within the first week after screening and, if they do not decide, again during the second week after screening (done by HiPP office, Belgrade)
- if the family is not interested in participation, this is recorded in the screening list and all personal information is deleted, but otherwise no further action is required
- only in case the family wants to formula feed / or does already feed formula and is interested in participation, the family is invited to the clinic for the baseline visit, an appointment is made and clinical personal is informed
- before the baseline visit the study is explained in detail
- after clarification of all open questions signature of informed consent (if parents decide not to sign this is recorded in the screening list and personal information is deleted)
- randomization and distribution of study formula with corresponding randomization number
- complete “subject identification list” and “subject randomization list”
- performance of baseline visit without blood sampling, but otherwise according to original protocol

# **Formula with modified content of protein and improved fatty acids and their impact on infant growth and health**

**Study nr.: 502042**

## **Amendment No.3**

### **Status Quo**

Aim of the BeMIM study was to provide a formula with a composition more similar to that of breast milk. The suitability of an infant formula with modified protein content and improved fatty acids for the particular nutritional use of healthy term infants was investigated against a standard formula (control). As hypothesized under the primary objective at the end of the intervention period there was no significant difference in weight gain between the control and the intervention group (data currently submitted to *Clinical Nutrition*). Based on these data it was concluded that the protein-reduced formula is suited for the exclusively feeding of healthy term infants.

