### 9.2 Hypothesis to be tested

$H_0$  (to be rejected): The mean daily weight gain in the intervention group (formula with reduced protein content) is more than 3 grams per day lower than in the control group (standard formula).

$H_{\text{alternative}}$ : The mean daily weight gain in the intervention group (formula with reduced protein content) is not more than 3 grams per day lower than in the control group (standard formula).

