### 9.3 Primary outcome variable

The main outcome variable "weight gain" will be calculated by subtracting the weight obtained at the 4 months study visit from the Visit 1 weight divided by the days passed between those visits.

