### 9.5 Sample size calculation

Based on previous publications and own data we can expect the children to grow on average 30 grams per day with a standard deviation of 6 grams between birth and 4 months of life. Growth studies should be designed to have a power to detect a difference in weight gain equal to 0.5 standard deviations according to the SCF report. Thus, one would need about 70 children in each formula group under the assumption of non-inferiority (one-sided test), a

significance level of 2.5% and a power of 85%. We expect a true loss-to follow-up of about 10-15%. Additionally, we expect that another 15% will switch formula due to preference changes which usually take place in the first months of life. These children will be only available for an intention-to-treat analysis. Thus, 100 children in each formula arm, as well as in the breastfed group will be included to have also sufficient power in a per-protocol analysis.

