### **9.9 Statistical analysis**

For all quantitative parameters determined a test for normal distribution will be performed according to Kolmogorov-Smirnov. If normal distribution can be assumed, mean and standard deviation will be given for these parameters. For non-normally distributed data median and interquartile range will be provided and data will be transformed appropriately prior to statistical analysis.

For the primary analysis breastfed children will not be included. They serve rather as a reference for the interpretation of the data collected in the formula groups.

The influence of the study group on the primary outcome will be tested using linear regression with baseline values as co-variables. Parameters, which might influence anthropometric development of the infant, e.g. gender, parental smoking and socio-economic status, will be tested for their effect on the outcome variable and, if appropriate, will be included as confounding factors.

Interim analyses are not foreseen as valuable results can not be expected from analysing the data from a limited number of subjects and an association of increased risk of occurrence of adverse events with any of the studied formulas is not conceivable.

Statistical analyses will be performed on the data collected from all infants enrolled into the study and randomised to one of the formulas (intention to treat analysis) and on the data collected from all subjects, who completed the study according to the protocol (per-protocol analysis). The per-protocol analysis is considered the primary analysis; the intention-to-treat analysis has confirmative character.

Full analysis (Intention-to-Treat = ITT Principal) comprises all subjects who were enrolled including those with minor and severe non-compliance to protocol, subjects with missing values (but who participated at least in Visit 1) and protocol violations. Solely subjects turned out to be a "screening failure" (does not fit to an important inclusion or exclusion criteria) will not be considered for full analysis.

The Per-Protocol Population (PPP) is defined as the set of subjects without severe non-compliance to the protocol. Minor non-compliance e.g. visit outside the given window, or missing values of marginal importance (stool colour not reported once) are acceptable and do not lead to exclusion from the PPP analysis.

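### Amendment No.3 reports a non-significant difference as the primary hypothesis and rests suitability on it, whereas 9.2 and 9.5 set a non-inferiority test against a 3 g/d deficit

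*Protocol*

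**What the plan says.** **Hypothesis and level.** Sections 3 and 9.1 make non-inferiority the primary objective. The null in 9.2, the one to be rejected, is that mean daily gain on the reduced-protein formula "is more than 3 grams per day lower than in the control group (standard formula"). The alternative is that it "is not more than 3 grams per day lower than in the control group". Section 9.5 expects infants to "grow on average 30 grams per day with a standard deviation of 6 grams", refers to "a difference in weight gain equal to 0.5 standard deviations", and arrives at "about 70 children in each formula group under the assumption of non-inferiority (one-sided test") with a 2.5% level and 85% power.

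**Analysis.** Section 9.9 states: "The influence of the study group on the primary outcome will be tested using linear regression with baseline values as co-variables". The per-protocol analysis is primary and the intention-to-treat analysis is confirmatory. Section 9.9 mentions no margin, confidence bound or direction. Section 9.10 applies the same methods to the secondary outcomes and refers to them as those of the primary hypothesis.

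**Outcome.** Section 9.3 computes the gain by "subtracting the weight obtained at the 4 months study visit from the Visit 1 weight", divided by the days between the two visits. Section 7.1 describes the outcome as average daily weight gain between Visit 1 and Visit 4.

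**Reported result.** Amendment No.3, Status Quo: "As hypothesized under the primary objective at the end of the intervention period there was no significant difference in weight gain between the control" (compared with the reduced-protein arm). The next sentence concludes from these data that the formula is suited for exclusive feeding of healthy term infants. It gives no estimate or interval and does not mention the 3 g/d margin.

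**The concern.** A non-significant difference and non-inferiority are different findings. The first says that the data do not exclude zero. The second says that they do exclude a deficit larger than 3 g/d. Fewer infants or noisier weights make the first easier to reach and the second harder. Amendment No.3 nevertheless presents the first as what the primary objective hypothesised.

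The regulatory purpose makes this matter. Sections 2 and 3 say that a formula below 2 g protein per 100 kcal needs an appropriate study to show suitability, and 13.3.2 foresees that the sponsor may submit results to EFSA. A reader who takes the Amendment at its word will think that suitability was to be judged by a rule that does not hold the 2.5% error rate for which the trial was sized.

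**Working it through.** **Inputs.** Margin 3 g/d (9.2); SD 6 g/d, one-sided 2.5%, power 85%, about 70 per formula arm (9.5); 100 recruited per arm with 30% loss (4.2, 9.5). Assumed: significance in Amendment No.3 means two-sided 5%, since no level is given there (one-sided 2.5% gives the same figure), and the comparison is unadjusted.

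**1. The plan's own figure.** n per arm = 2 × [SD × (z0.975 + z0.85) / margin]² = 2 × [6 × (1.960 + 1.036) / 3]² = 71.8, so 72. Power at 70 per arm is 84.1%. 70 / (1 − 0.30) = 100. The stated size of about 70, and 100 recruited, reproduces for a non-inferiority test with a true difference of zero.

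**2. The two rules at 70 per arm.** SE = 6 × √(2/70) = 1.014 g/d, and 1.96 × SE = 1.99 g/d.
- Non-significance tolerates an observed deficit up to 1.99 g/d.
- Non-inferiority (lower 95% limit above −3) tolerates one up to 3 − 1.99 = 1.01 g/d.
- An observed deficit between about 1.0 and 2.0 g/d is therefore non-significant but fails the test in 9.2.

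**3. Chance of passing when the true deficit is exactly 3 g/d.** Non-inferiority rule: 2.5% by construction. Non-significance rule: Φ(1.96 − 3/SE), where the opposite tail is negligible. At 70 per arm this is Φ(1.96 − 2.958) = Φ(−0.998) = 15.9%. With the noncentral t it is 16.4%.

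| Analysed per arm | SE (g/d) | Passes, normal | Passes, t |
|---|---|---|---|
| 70 (planned per protocol) | 1.014 | 15.9% | 16.4% |
| 85 (100 less 15% lost to follow-up) | 0.920 | 9.7% | 10.0% |
| 100 (all recruited) | 0.849 | 5.8% | 6.0% |

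The SD matters as much. At 70 per arm, with other SDs taken as assumptions, the normal figure is 5.6% at SD 5, 28% at SD 7 and 40% at SD 8.

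**4. The sign in 9.3.** Take gains of 30 g/d (control) and 27 g/d (intervention) over the 90 days from day 30 to day 120. Visit 1 weight minus Visit 4 weight, divided by 90, gives −30 and −27. The intervention arm then appears 3 g/d higher, so the wording *lower than control* in 9.2 points the wrong way.

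**The case against.** A reader might infer that the plan itself analyses the question as a test of no difference. The documents do not support that. Sections 9.2 and 9.5 fix the margin, the direction and the level. Section 9.9 names a model and nowhere states a null of zero, and the confidence limit of its group coefficient is exactly what 9.2 needs. Section 9.10 links these methods to the primary hypothesis. It also extends them to outcomes without a margin, where only a comparison with zero is possible, but that does not settle how the primary test is done. Naming the bound is a detail that a statistical analysis plan could supply.

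A reader might also infer that the comparison with −3 g/d was never made. Amendment No.3 does not show that. The sentence is background in an amendment that adds visits around the fourth and sixth birthdays, and it points to a manuscript that is not at hand. The 16% is therefore not an operating characteristic of the written plan. It is what the sentence would imply if used as the rule. It also falls with more infants, or with a smaller residual SD after covariate adjustment.

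On 9.3, section 7.1 and the expected gain of 30 g/d make the intended direction clear, so this is an editorial slip.

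All of that stands, and it narrows the point. What remains is that the sentence is not a description of superseded text. It is the protocol's own current account of the primary hypothesis and of the basis for suitability, and it disagrees with 9.2. A separate analysis plan would not correct it.

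**Conclusion.** The point holds for Amendment No.3, which misstates the primary hypothesis and draws the suitability conclusion from the misstatement. Used as a rule, it would accept a formula at the 3 g/d limit about 16% of the time rather than 2.5%, given 70 analysed per arm, SD 6, an unadjusted comparison and two-sided 5%. The excess shrinks to about 6% against 2.5% if all 100 per arm are analysed. For 9.9 the defect is only that the regression is not tied to the margin; for 9.3 it is a reversed subtraction. Nothing here shows that the trial's conclusion is wrong. This should be fixed, but it does not invalidate the design.

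**What to change.** - **Amendment No.3, Status Quo:** replace the sentence on no significant difference with the estimated difference in mean daily gain (intervention minus control), its 95% CI and the comparison with −3 g/d. Base the suitability statement on that comparison.
- **Section 9.9:** add that non-inferiority is concluded if the lower limit of the two-sided 95% CI for the group coefficient (intervention minus control) in the primary per-protocol model lies above −3 g/d, with the intention-to-treat interval reported beside it.
- **Section 9.3:** define the outcome as (Visit 4 weight minus Visit 1 weight) divided by the days between the visits.

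The cost is wording in three places. The interval comes from the regression already planned, and no new data or change of sample size is needed.
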